**Figure 3 figure3:**
[figure not shown]
The direct acyclic graph of the Bayesian model acts like a causal diagram. In the model, the explanatory variables {X1, . . . , X6}: age, sex, BMI, pain intensity, weight-bearing status, and initial injury severity. These variables causally affect the subject-specific slopes and the y-intercepts. However, the slopes and y-intercepts of the responses are not directly observed, so they are considered latent variables. In the diagram, the shaded circles are directly observed variables, and the unshaded circles are latent variables. The Bayesian model has 2 levels of hierarchy: the first one establishes the best fit line that goes through the observed subject responses; the second one establishes how the explanatory variables {X1, . . . , X6} affect the slopes and y-intercepts. The regression parameters {η_0_, . . . , η_6_} are those that affect the slope of the subject responses and, as such, are particularly important because they affect the healing rate. Variables that significantly affect the healing rate will be retained in the model if the credible intervals for the regression parameters {η_0_, . . ., η_6_} do not include 0.

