Based on the burden and morbidity associated with LAS and CAI, proper management of these injuries is especially salient in service members. This population has high physical demands and esoteric occupational and environmental exposures that increase injury risk [2]. Clinical practice guidelines for the treatment of LAS recommend inclusion of early progressive weight bearing, manual therapy, and functional exercises that include proprioceptive balance training [16]. These updated guidelines further recommend these exercises for secondary prevention of subsequent injury and outline the necessity for graded exposure to occupational-related tasks [16]. Proprioceptive training has been shown to improve some of the postural control deficits and COP excursions in patients with LAS and CAI [11] and to decrease the risk of reinjury [7,16]. Provision of therapeutic exercises, including proprioceptive training, early in the rehabilitation course has been shown to be prophylactic during the first 12 months following LAS [7].

Despite the demonstrated benefits of proprioceptive training and early rehabilitation following LAS, there is no evidence to suggest that the burden of CAI is decreasing. Currently, most proprioceptive training encompasses the use of static balance exercises performed on solid and compliant surfaces [17]. While static exercises are indeed important as part of a comprehensive rehabilitation course, they have limited ecological validity and may not provide the specificity needed to prepare service members for environmental hazards frequently encountered in the performance of occupational duties. Treatment modalities that provide graded exposure to perturbations during functional activity may better help to facilitate sensorimotor plasticity and integration in preparation for return to duty [11]. The purpose of this pragmatic randomized controlled trial is to determine if incorporation of graded exposure on an uneven-terrain treadmill during standard rehabilitation care will lead to greater improvement in function and secondary preventive effects than standard rehabilitation care alone in military service members with LAS and CAI up to 18 months following treatment. The secondary aim of this is to identify the factors that predict and mediate treatment outcomes in this population.

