### Statistical Analysis

To assess whether the addition of the rocky treadmill intervention to standard-of-care physical therapy improves rehabilitation, 4 repeated measurements of several outcomes (eg, CAIT and FAAM) will be measured over the active intervention period of the study. The data will be analyzed using an analysis of covariance–type linear mixed-effects model with Group, Time, and Group×Time variables as fixed effects and subject-specific variables {intercepts, slopes} as random effects. The null hypotheses for both LAS and CAI populations are that the slopes of the control groups equal those of the treatment groups.

To identify predictors and mediators of successful or unsuccessful rehabilitation outcomes, a 2-level (hierarchical) Bayesian model will be used to connect participant-specific responses to 6 explanatory variables: {X1, . . . , X6} = {age, sex, body mass index, pain intensity, weight-bearing status, and initial injury severity} to the subject-specific variables {intercepts, slopes}. A directed acyclic graph detailing the results of the Bayesian linear model will be developed (Figure 3). The regression parameters from the hierarchical Bayesian model will be estimated using Bayesian inference with Gibbs Sampling software, which creates a Markov chain Monte Carlo simulation of all regression parameters.

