To analyze the effect of the treatment on long-term reinjury rates between the 2 arms of the study, we will fit both logistic regression–type generalized linear mixed-effects (GLME) models to the data as well as Cox regression time-to-event models. The data that will be used in the analysis will be those obtained at baseline and during the postintervention period. In the GLME analysis, the response data will be (1) the self-reported survey instrument measure from the Patient-Reported Outcomes Measurement Information System and (2) the binary reinjury report (1/0). The GLME model will have Group, Time, and Group×Time as fixed effects and will use subject-specific variables {intercepts, slopes} as random effects. The null hypothesis of the GLME model is that the regression parameters associated with the Group and Group×Time effects are zero. In the Cox regression analysis, the response will be the time of suspension or the event along with a binary indicator of reinjury status, and the covariate will be Group. The null hypothesis of the Cox regression analysis is that the regression parameter associated with Group is equal to zero. In all analyses, a Bonferroni-type correction to the hypothesis test’s *P* values or α levels will be used to account for multiple testing.

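### Predictors of healing rate are kept only if their own credible interval excludes 0; this filter overstates weak effects, alters the remaining coefficients, and is not tied to the promised multiplicity correction

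*Protocol article*

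**What the plan says.** The Introduction of the protocol article sets the aim: "The secondary aim of this is to identify the factors that predict and mediate treatment outcomes in this population". The Statistical Analysis section assigns the method: "To identify predictors and mediators of successful or unsuccessful rehabilitation outcomes, a 2-level (hierarchical) Bayesian model will be used". Its second level relates each participant's intercept and slope to six explanatory variables: "age, sex, body mass index, pain intensity, weight-bearing status, and initial injury severity".

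The legend of Figure 3 gives the decision rule: "Variables that significantly affect the healing rate will be retained in the model if the credible intervals for the regression parameters" η0 to η6 exclude 0. The legend states no credible level or prior. It describes the graph as acting like a causal diagram and says the six variables causally affect the slopes and intercepts.

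On multiplicity, the Statistical Analysis section says, after describing the models: "In all analyses, a Bonferroni-type correction to the hypothesis test’s" P values or to the α "levels will be used to account for multiple testing".

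Two further statements concern the linear mixed model, not the Bayesian one. It is to be applied to several outcomes: "4 repeated measurements of several outcomes (eg, CAIT and FAAM) will be measured over the active intervention period of the study". It has a null hypothesis for each injury type: "The null hypotheses for both LAS and CAI populations are that the slopes of the control groups equal those of the treatment groups".

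**The concern.** Retaining a coefficient only when its interval excludes 0 is significance selection, even when the interval is Bayesian. Three consequences follow.

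- **Exaggeration.** With limited precision, a weak true effect passes the filter only when chance has pushed its estimate upwards. The retained estimates are therefore too large on average.
- **Changed meaning.** Each coefficient is adjusted for the other variables in the model. If age is dropped because its interval includes 0, the body mass index coefficient is no longer adjusted for age. A causal reading needs the adjustment set chosen on subject-matter grounds, not by which intervals happened to include 0.
- **Unconnected error control.** The multiplicity sentence corrects P values and α levels. The retention rule uses neither, so the reader cannot tell whether or how the correction applies to it.

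The rule also lists η0, which is not tied to any of the six variables. In the usual notation it is the intercept of the slope equation.

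At stake is the reliability of the secondary aim: which factors are reported as driving recovery, and how large their effects are said to be.

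**Working it through.** The article gives no error rate, credible level or sample size for the predictor analysis, so there is no stated figure to reproduce.

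**Inputs from the article.** Six predictors (Statistical Analysis); 156 participants per injury stratum (Recruitment); one interval per coefficient (Figure 3 legend).

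**Assumptions, not in the article.** 95% intervals; priors weak enough that the interval behaves like a two-sided .05 test; a fit within one stratum; participant slopes treated as the response, with residual SD 1; predictors standardised with pairwise correlation 0.3.

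**Step 1. False retention when no predictor has an effect.**

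- Independent estimates: 1 − 0.95^6 = 0.265, with 6 × 0.05 = 0.3 false predictors expected per model. Simulation at n = 156 gave 0.26 to 0.27.
- Equicorrelated estimates: about 0.21 at correlation 0.5 and 0.14 at 0.8.
- Bonferroni carried over to the intervals: level 1 − 0.05/6 = 99.17%, giving 1 − (1 − 0.05/6)^6 = 0.049.

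**Step 2. Exaggeration of a true effect that is retained.**

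The variance inflation factor for six predictors at correlation 0.3 is (1 + 4 × 0.3) / [(1 − 0.3)(1 + 5 × 0.3)] = 2.2/1.75 = 1.257. The standard error is about √(1.257/149) = 0.092, with 149 = 156 − 7 residual degrees of freedom.

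For a true effect β, let δ = β/0.092, and let c be the critical value (1.976 at 95%). Ignoring the negligible lower tail, the mean retained estimate divided by the truth is [φ(c − δ) + δ(1 − Φ(c − δ))] / [δ(1 − Φ(c − δ))].

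For β = 0.15: δ = 1.633 and c − δ = 0.343, so φ = 0.376 and 1 − Φ = 0.366. The ratio is (0.376 + 1.633 × 0.366) / (1.633 × 0.366) = 0.974/0.598 = 1.63. The chance of retention is about 37%.

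Simulation of the full regression (4,000 replicates, n = 156 per stratum) gave:

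| True standardised effect | Retained at 95% | Exaggeration at 95% | Exaggeration with Bonferroni over 12 intervals |
|---|---|---|---|
| 0.10 | 20% | 2.30 | 2.98 |
| 0.15 | 36% | 1.63 | 2.03 |
| 0.20 | 58% | 1.30 | 1.58 |
| 0.30 | 90% | 1.06 | 1.18 |

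The last column takes 12 intervals, that is, six predictors in each of two strata. For six intervals only, c = 2.674. The same formula for β = 0.15 has c − δ = 1.041, φ = 0.232 and 1 − Φ = 0.149, giving (0.232 + 1.633 × 0.149) / (1.633 × 0.149) = 0.475/0.243 = 1.95. A stricter filter lowers false retention and raises exaggeration, whichever count is used.

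**Step 3. Further multiplicity, conditional only.** If the Bayesian model were fitted separately in both strata, the uncorrected chance of any false retention would be 1 − 0.95^12 = 0.46. With two outcomes as well it would be 1 − 0.95^24 = 0.71 if independent, or 0.64 to 0.67 in simulation with outcomes correlated at 0.6. The article states neither kind of separate fit for this model.

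**The case against.** The strongest reply is that the article does promise control: the multiplicity sentence covers all analyses, and an α-level correction translates readily into a wider credible interval. That stands. A reader might infer that the predictor search has no multiplicity control at all; the text does not support this. What remains is that the correction is not linked to the retention rule, and that even if it were, exaggeration would rise rather than fall.

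A reader might also infer that the search runs over two strata and several outcomes, with a false-predictor rate of 46% to 71%. The article says this only of the linear mixed model, so those figures are conditional and are not part of the finding.

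Third, the credible level and prior are details an article may leave to an analysis plan, and a shrinkage prior would reduce both false retention and exaggeration. That also stands: their absence is not raised here, and the 26% is an illustration under stated assumptions. The retention rule, however, is stated in the article. A shrinkage prior would not undo the change in meaning when covariates are dropped.

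Fourth, listing η0 may be shorthand for all coefficients of the slope equation, since no variable attaches to it. That is plausible; it needs only a clarifying word.

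Finally, strong effects are hardly inflated (1.06-fold at 0.30), and this is a secondary aim. Both are correct and limit the weight of the point.

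**Conclusion.** The point holds in limited form. The stated rule is a one-at-a-time significance filter that decides the secondary aim. It overstates weak retained effects, by about 1.6-fold for a true standardised effect of 0.15 at n = 156 but only about 1.06-fold for 0.30. It also changes the adjusted meaning of the remaining coefficients in a model presented as causal.

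False retention depends on how the multiplicity sentence is read. It is about 26% for six null predictors with uncorrected 95% intervals and weak priors, 14% to 21% if the estimates are strongly correlated, and about 5% if Bonferroni is carried over to the intervals. All of these rates also assume that none of the six variables has an effect. The documents therefore do not support saying that the trial will often report false predictors; they support saying that the rule leaves this open and biases what it keeps.

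The primary FAAM comparison, the reinjury analyses and the sample size are not affected.

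**What to change.** Delete the retention rule from the Figure 3 legend. Keep all six predictors and the intercept η0 in the model, report every posterior estimate with its interval, and label the predictor findings exploratory. This removes the selection bias however the multiplicity sentence is read. Six predictors are easily supported by 156 participants per stratum.

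If any predictor is still to be declared significant, state that the Bonferroni-type correction applies to the credible level and over how many intervals (99.17% for six). The full model should be reported even then, because the correction does not cure exaggeration.

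A common shrinkage prior on η1 to η6 is an optional refinement, not a requirement.

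Cost: a few lines of wording and model code, with no new data. The downside is slightly wider intervals than in a reduced model, and more cautious wording of the predictor results.

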### Power and Sample Size

The estimated sample to identify a minimum difference of 1 point in the FAAM between treatment groups across 4 time points in the intervention period was 17 participants per group for an estimated power of 90% and an α value of .05. To measure the effect of the long-term binary reinjury rates with 6 time points in a GLME model, a sample of 62 participants per group provided 80% power, assuming a 10% difference in the proportion between the treatment groups and similar trends between groups. Assuming a 20% rate of dropout throughout long-term follow-up, the required sample size is 78 participants per group. Between the 2 injury types (LAS and CAI), a total of 312 participants will be recruited for this study across the multiple sites.

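### The reinjury power that sets the sample size is stated without the Bonferroni correction the plan applies in all analyses; if it used two-sided .05, the 80% is at most about 71%

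*Protocol article*

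**What the plan says.** The protocol article, under Power and Sample Size, gives two calculations.

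- **FAAM:** 17 in each arm, to detect a 1-point difference over the 4 measurements of the intervention period, sized "for an estimated power of 90% and an α value of .05".
- **Reinjury:** for a GLME model of the 6 follow-up assessments, "a sample of 62 participants per group provided 80% power". The effect assumed is a 10% difference in proportions, with trends alike in the two arms. No significance level is given here.

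The reinjury figure is then carried into recruitment: "Assuming a 20% rate of dropout throughout long-term follow-up, the required sample size is 78 participants per group". Two groups in each of two injury types give the total of 312.

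The Statistical Analysis section sets the decision rule. For the outcomes of the intervention period, "The null hypotheses for both LAS and CAI populations are that the slopes of the control groups equal those of the treatment groups". For long-term reinjury it plans both a GLME model (null hypothesis on Group and Group×Time) and a Cox model (null hypothesis on Group). The paragraph on reinjury closes with the multiplicity rule, which begins "In all analyses, a Bonferroni-type correction to the hypothesis" and allows the adjustment to be made to P values or to α levels. The article does not say how many tests are counted, and the power section does not mention a correction.

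**The concern.** A power figure describes a test at a particular significance level. Here the only level used for sizing is .05, and the rule for testing is stricter than .05 by some unstated factor. If the reinjury calculation used the one level the section mentions, then 80% is not the power of the test that will be run.

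This matters because the reinjury calculation alone sets the recruitment target, and it has no reserve beyond the dropout allowance. Lower risk of reinjury is also one of the trial's stated hypotheses. A non-significant reinjury result would be read against an advertised 20% chance of missing the assumed difference, when the chance under the plan's own rule would be 29% or more.

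**Working it through.** **Inputs from the article.** FAAM: 1 point, 17 per group, 90% power, α .05. Reinjury: 62 per group, 80% power, 10% difference in proportion, 6 time points, 20% dropout, 78 per group, 312 in total.

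**Inputs assumed.** Tests are two-sided. The reinjury calculation used .05. The number of tests k is not given, so a range is shown.

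**1. The plan's own figures.** 62 / 0.80 = 77.5, rounded up to 78; 4 × 78 = 312. Both reproduce. The 17 and the 62 cannot be derived independently, because the article gives no SD or within-subject correlation for the FAAM and no control rate or correlation for reinjury.

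**2. Smallest possible k.** A Bonferroni correction over one test is no correction, so the rule implies k ≥ 2. The text supplies two tests on more than one reading: the LAS and CAI strata, each sized as its own comparison, or the GLME and Cox tests of reinjury within a stratum.

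**3. Reinjury power at the corrected level.** The missing control rate and correlation are not needed if the signal strength implied by 62 per group and 80% power is held fixed:

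- implied noncentrality = z(.975) + z(.80) = 1.960 + 0.842 = 2.802
- power = Φ(2.802 − z(1 − .05/(2k)))
- evaluable n for 80% = 62 × [(z(1 − .05/(2k)) + 0.842) / 2.802]², rounded up
- recruited n = evaluable n / 0.80, rounded up

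| k | critical z | power at 62 per group | evaluable per group for 80% | recruited per group at 20% dropout |
|---|---|---|---|---|
| 1 | 1.960 | 80% | 62 | 78 |
| 2 | 2.241 | 71% | 76 (75.1) | 95 |
| 3 | 2.394 | 66% | 83 | 104 |
| 4 | 2.498 | 62% | 89 (88.1) | 112 |

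For k = 2: Φ(2.802 − 2.241) = Φ(0.561) ≈ .71. The chance of missing the assumed difference goes from 20% to 29%, and to 38% at k = 4.

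If nobody dropped out, the noncentrality at 78 per group would be 2.802 × √(78/62) = 3.143. Power would then be 82% at k = 2, 77% at k = 3 and 74% at k = 4.

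**4. FAAM power at the planned size.** At 17 per group the implied noncentrality is 1.960 + 1.282 = 3.242. At 62 per group it is 3.242 × √(62/17) = 6.19. Even with k = 20 (critical z 3.02), power is Φ(6.19 − 3.02) = Φ(3.17), which is above 99.9%. At 78 per group it is higher still.

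**The case against.** **The .05 is not stated for reinjury.** This is correct: it stands in the FAAM sentence only. Nor can the reported 62 settle the matter. With the usual repeated-measures factor (1 + 5ρ)/6, a 20% versus 10% comparison needs 199 per group at one time point at two-sided .05, and gives 62 with ρ about 0.17. At .025 it needs 242, and gives 62 with ρ about 0.11. A corrected level therefore cannot be ruled out. It remains the less natural reading, since the section mentions one level and no correction, but the finding has to be conditional.

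**The family of tests belongs in an analysis plan.** This also stands: its absence from the article is not the point here. The point is that two statements in the article, one on sizing and one on testing, do not use the same level.

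**The rule might not pool LAS and CAI.** Possibly, but the correction sentence closes the paragraph on the reinjury models and covers all analyses. Some correction of the reinjury tests is therefore planned on any plain reading.

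**Stronger readings that the document does not support.**

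- A reader might infer that the primary FAAM comparison loses power, to 84% for two tests or 77% for four. Those values hold only at 17 per group, and the trial plans 62 to 78.
- A reader might count six reinjury tests, or spread the correction over every clinical and biomechanical measure. The article does not define the family that way. The GLME null can be read as one joint hypothesis, and a correction in all analyses can mean within each analysis. Only k ≥ 2 is secure.

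**Conclusion.** The inconsistency is real and confined to reinjury. The article sizes at an uncorrected level, so far as it states one, and tests at a corrected level. If the reinjury calculation used two-sided .05, its power at 62 evaluable per group is at most about 71% under the plan's own rule, and about 62% if four tests are counted, against the stated 80%. These figures rest on the assumed starting level, on the implied effect being held fixed, and on k, which the article does not give.

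The FAAM, the named primary outcome, is unaffected in practice, on the effect size and variability that 17 per group implies. The recruitment arithmetic is also correct. This should be fixed because the figure that justifies the sample size is misstated for its test, but it does not undermine the primary comparison.

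**What to change.** - State the significance level and sidedness used for the reinjury calculation.
- State which tests the Bonferroni-type correction covers and how many there are. Keep the set small, but include the FAAM and one reinjury contrast per stratum, saying which reinjury model and parameter is meant and how the FAAM subscales are counted.
- Restate the reinjury power at the corrected level for the planned 62 evaluable per group. One FAAM test and one reinjury contrast in each of two strata, taken as a single family, make four tests and about 62%. Correcting over two tests only gives about 71%.

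Reducing the confirmatory set to one FAAM subscale alone is not needed to cure this defect, and it would drop the reinjury hypothesis on which the trial was sized.

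The cost is a change of wording and a lower stated power. No added enrolment is required. If the sponsor wished to hold 80% instead, the price would be about 95 recruited per group for two tests (4 × 95 = 380) or 112 for four (4 × 112 = 448), against 312 planned.
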